### Analysis

Data analysis was performed using the Statistical Package for Social Science software, version 20.0 for Windows. When assessing the effectiveness of interventions between the two groups, we will first compare the baseline characteristics of the patients using chi-square test for categorical variables and *t*-test or Wilcoxon rank-sum test for continuous variables between the experimental and control groups. The primary analysis will be an unadjusted intention-to-treat analysis of the difference in self-reported 7-day point prevalence quit rate of the smoking cancer patients during 6-month follow up between the two groups. The analysis will be performed using Pearson’s chi-square test or with the use of Fisher’s exact test, if there were five or fewer participants per cell. Similar approach will be used to estimate the differences in secondary outcomes (e.g. self-reported 7-day PP quit rate at 12-month follow-up and the biochemically validated quit rate at 6-month follow-up, percentage of patients reduced smoking by at least 50 % at 6- and 12-month follow-up compared to baseline, and quality of life at 6 and 12 months) between groups. Crude odds ratios (ORs) for quitting will be estimated using logistic regression model and were compared with ORs that were adjusted for baseline variables (e.g. sex, age, education, stage of readiness). Those who are lost to follow-up or refuse to participate in the validation tests, will be treated as smokers with no reduction in cigarette consumption compared with (a) baseline, as the main analysis (by intention to treat), (b) the most recent level and (c) complete case (per protocol) analysis by excluding subjects with missing data as a sensitivity analysis.

For the process evaluation, all qualitative data from interviews will be tape-recorded and transcribed verbatim. Content analysis will be employed and themes identified. The constant comparative method will be used to search for common constructs and themes about the implementation and the effect of the intervention as perceived by the participating subjects.

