### Randomisation

Randomization will be done with each session in an out-patient clinic as a cluster unit. Currently there are 10 sessions per week per study site. Before the study, we will randomly draw the sessions by computer generated random sequence (block randomization with each hospital as a block unit), so that 5 sessions will be treated as intervention group and another 5 sessions will be treated as control group per week. Participants who consent to participate in the study will be assigned to either intervention or control group depending on the out-patient clinic session that they are seeking consultation. By using this experimental design, we can ensure similar proportion of smoking cancer patients will fall into the intervention and control group in each out-patient clinic, and each out-patient clinic will have a similar proportion of cancer patients into the intervention/ control group. We expect the intervention and control group would have similar socio-demographic profile, smoking history, and clinical history and we shall check for any differences, and if any, we shall adjust for them in the analyses. In using the cluster randomization design with a session being a cluster unit, the patients who are randomized into the experimental and control groups would have less chance to meet each other in the out-patient clinic and discuss the contents of the smoking cessation interventions.

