### Measures

#### Structured questionnaire

A structured questionnaire will be developed by adopting or modifying international and/or locally validated instruments. The questionnaire gathers information including smoking and quitting history, risk perceptions of smoking [23], illness perception [24], intention to quit smoking (stage of readiness to quit) [21], antecedent factors of the TPB model (behavioral beliefs, outcome evaluations, normative beliefs, motivation to comply) [25], pros and cons of smoking (decisional balance), self-efficacy to resist smoking [26], quality of life (SF-12 v2) [27], other lifestyle risk factors (drinking, physical activities, and fruit and vegetable intake), demographic information such as age, gender, and marital status, and clinical information including height, body weight, body mass index, time to diagnose cancer, stage of cancer, number of tumor sites, blood pressure, and history of surgery, radiotherapy and chemotherapy. The demographic and clinical information will be obtained from the medical records.

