### Power calculation

Sample size is calculated by “Power Analysis and Sample Size (PASS) v. 13” (http://www.ncss.com/pass.html) and based on the main outcome variable according to the main hypothesis, the 7-day point prevalence self-reported quit rate at 6-month in the experimental group is higher than the control group. A previous RCT study [28] conducted in Australia, which applied motivational intervention to 137 smoking patients with mixed cancer sites. Based on that study, the self-reported 7-day point prevalence quit rate at 6-month follow up was 29 % for the intervention group and 18 % for the control group. To detect a statistical difference at 5 % significant level and a power of 0.8, 233 patients will be needed in each of the 2 groups (based on independent samples Fisher exact test). With reference to the local RCT on smoking cessation intervention for cardiac patients [22], we assume a 15 % attrition rate at the 6-month, and 274 patients will be required in each group to achieve a significant outcome. Accounting for the clustered randomized sampling design with 20 clusters (sessions) and an intra-class correlation of 0.002, 280 patients will be required per group, adding up the total sample size to 560 from the experimental and control groups together.

From the information provided by our clinical partners on site screening, there are around 2000 new patients per hospital per year. According to our previous qualitative study [23] conducted in an out-patient clinic on Chinese current smokers and ex-smokers, about 13.7 % patients continued smoking after receiving a cancer diagnosis (274: 13.7 % of 2,000). However, more than 50 % of these smokers were reluctant to quit (137: 50 % of 274). In a rough estimation, there will be around 700 eligible subjects in five acute Hospital Authority hospitals each year. We have confidence that we can recruit adequate subjects (560) according to the power analysis within an 18-month (78-week) recruitment period.

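### The primary comparison is fixed as unadjusted although baseline stage of readiness to quit is already collected; this is valid, but it forgoes modest precision at no saving

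*Protocol article*

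**What the plan says.** All references are to the protocol article.

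- **Analysis.** The primary result is fixed as follows: "The primary analysis will be an unadjusted intention-to-treat analysis", applied to the group difference in self-reported quit rate at 6 months. The test is also named: "The analysis will be performed using Pearson’s chi-square test or with the use of Fisher’s exact test", the latter for small cells. Patients lost to follow-up count as smokers. Crude odds ratios from logistic regression are then set beside "ORs that were adjusted for baseline variables (e.g. sex, age, education, stage of readiness", a list opened by an e.g. and so not closed.
- **Randomisation.** On baseline differences between the groups: "we shall check for any differences, and if any, we shall adjust for them in the analyses".
- **Structured questionnaire.** The instrument covers "intention to quit smoking (stage of readiness to quit" among its items. The Procedure section has the baseline questionnaire completed before the intervention.
- **Study sample and recruitment.** No inclusion or exclusion criterion concerns readiness. Table 1 scripts counselling for pre-contemplation, contemplation and preparation.
- **Conceptual framework.** The antecedents of quitting are taken to act through intention.
- **Power calculation.** 233 per group for 29 % against 18 %, then 274 for attrition and 280 for clustering. Of patients still smoking after diagnosis, "more than 50 % of these smokers were reluctant to quit".

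**The concern.** A baseline variable that predicts the outcome can sharpen the treatment comparison if it enters the analysis by a rule set in advance. Here the protocol measures such a variable before treatment, builds its theory and its stage-matched counselling on it, and names it as a covariate, yet keeps it out of the primary result.

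Two things are at stake. One is precision: the crude difference carries variation between stages that a standardised difference would remove, while both estimate the same marginal difference in quit rates. The other is what happens if the groups differ in readiness by chance. The crude primary result would carry that difference. The planned answers are an adjusted odds ratio with an unfinished covariate list and a promise to adjust for whatever imbalance is found. Neither settles in advance which adjusted result counts.

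**Working it through.** **1. Reproduce the stated size.** Inputs from the Power calculation section: p1 = 0.29, p2 = 0.18, alpha 0.05 (taken as two-sided), power 0.80.

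n = [1.96·√V0 + 0.8416·√V1]² / (p1 − p2)²

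- V0 = 2 × 0.235 × 0.765 = 0.3596
- V1 = 0.29 × 0.71 + 0.18 × 0.82 = 0.3535
- n = (1.1752 + 0.5004)² / 0.0121 = 232.05, so **233**, as stated

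Power at 233 is 0.802. So the unadjusted chi-square comparison delivers the planned 80 % on the plan's own rates.

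**2. Adjusted comparison, three stages.** The documents do not say how strongly stage predicts quitting or how those enrolled divide among stages. Assumptions: a 50/30/20 mix from least to most ready; three sets of control quit rates; a common odds ratio for treatment across stages; overall rates held at 18 % and 29 %. Within-stage variances replace the overall ones:

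- V1 = Σ w·[pC(1 − pC) + pT(1 − pT)]
- V0 = Σ w·2·p̄(1 − p̄)
- power = Φ{[0.11 − 1.96·√(V0/n)] / √(V1/n)}

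Middle setting: control 8/22/37 %, treated 14.8/36.0/54.0 %.

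V1 = 0.5(0.0736 + 0.1261) + 0.3(0.1716 + 0.2304) + 0.2(0.2331 + 0.2484) = 0.3168, and V0 = 0.3237.

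Variance ratio = 0.3168 / 0.3535 = 0.896. Power at 233 = Φ[(0.11 − 0.0731) / 0.0369] = 0.842.

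| Assumed prediction | Control rates by stage | Variance falls by | Power at 233 (crude 80.2 %) | Power at 280 (crude 86.8 %) |
|---|---|---|---|---|
| Weak | 12 / 21 / 28.5 % | 3.5 % | 81.5 % | 88.0 % |
| Middle | 8 / 22 / 37 % | 10.4 % | 84.2 % | 90.1 % |
| Strong | 6.2 / 22.6 / 40.7 % | 14.8 % | 85.9 % | 91.5 % |

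The strong row is 7/25/44 % shifted on the logit scale, because those rates average 19.8 % on this mix rather than 18 %.

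The formula treats the stage mix as known. Estimating it adds little. In the middle setting the stage-specific differences are 6.8, 14 and 17 points, with variance 0.5 × 0.042² + 0.3 × 0.03² + 0.2 × 0.06² = 0.0019. Half of that is 0.0009, or about 0.3 % of 0.3168.

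**3. Sensitivity to the mix, two levels (ready or reluctant), 233 per group.** Same formula, with an assumed odds ratio for quitting, ready against reluctant, of 2 to 6.

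| Share ready | Power (crude 0.802) | n per group for 80 % |
|---|---|---|
| 50 % | 0.810 to 0.846 | 228 to 207 |
| 80 % | 0.806 to 0.818 | 230 to 223 |
| 95 % | 0.803 to 0.806 | 232 to 230 |

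**4. Missing counted as smoking.** With the plan's 15 % attrition, the rates become 0.85 × 29 = 24.65 % and 0.85 × 18 = 15.3 %. The effective size is 280 / 1.0254 ≈ 273, where 1.0254 = 1 + (274/20 − 1) × 0.002. Crude power is then 0.782. Adjustment with an even split and odds ratio 2 to 6 gives 0.789 to 0.822.

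**5. Chance imbalance, as illustration only.** Moving 10 % of one group from the lowest to the highest stage in the middle setting shifts its expected quit rate by 0.10 × (0.37 − 0.08) = 2.9 points. With 280 per group allocated individually, the between-stage variance is 0.5 × 0.08² + 0.3 × 0.22² + 0.2 × 0.37² − 0.18² = 0.0127. The SD of the chance difference is √(2 × 0.0127 / 280) = 0.95 points, so 2.9 points or more in either direction occurs in about 0.2 % of trials.

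**The case against.** The strongest reply is that this is a preference. An unadjusted comparison of two proportions is a legitimate primary analysis, it matches the way the trial was sized, and it reaches the stated 80 %. An odds ratio adjusted for readiness is already planned beside the crude one, so readers will see it. All of that stands: the test is valid, and what is lost is efficiency.

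Three stronger readings are tempting, and the documents do not support them.

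- *The trial population is split about in half on readiness.* The figure describes patients found still smoking after diagnosis in an earlier study. The eligible count of around 700 a year matches 5 × 137 = 685, so the reluctant half appears to have been taken out. Yet no criterion excludes reluctant smokers, and Table 1 provides for pre-contemplators. The enrolled mix is simply unknown.
- *Readiness is an established strong predictor in this trial.* The framework assumes that intention leads to quitting, but no figure for its strength is given. With weak prediction, or with most patients ready, the gain is close to nil.
- *A large chance imbalance is to be expected.* Under individual allocation the 10-point example is rare. Drawing sessions rather than patients would raise the chance, but the documents do not allow the amount to be worked out, and sessions are balanced five to five within each hospital.

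The calculations above also leave session clustering out of the adjusted variance, so they do not themselves validate a clustered standard error.

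**Conclusion.** The point holds as an avoidable loss of efficiency in a valid plan. The primary result leaves out a baseline variable that is already collected, that the plan itself names as a covariate, and that its own framework places on the path to quitting. Standardising over stage keeps the same marginal quit-rate difference.

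The likely size is modest. Variance falls by about 3 to 15 % and power at 233 per group rises by about 1 to 6 points under the assumed 50/30/20 mix and weak to strong prediction. The gain is about 0 to 1.6 points if 80 to 95 % of those enrolled are ready to quit. Both the mix and the predictive strength are assumptions.

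The part that does not depend on them is the wording: adjustment rests on an open list in one section and on observed imbalance in another, and a single covariate named in advance would settle it for the primary result.

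**What to change.** Before outcome data are seen by group, amend the Analysis section so that:

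- the primary estimate is the difference in 6-month self-reported quit rate standardised over baseline stage of readiness: a logistic model with group, stage and hospital, its predictions averaged over all randomised patients under each group, with standard errors that allow for clustering by session;
- missing outcomes count as smoking, as already planned;
- the crude difference is kept as a supporting result;
- the covariates of the primary model are listed in full, without an e.g.;
- the statement in the Randomisation section about adjusting for differences found no longer applies to the primary result.

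The sample size need not change. The cost is plan wording, slightly more analysis work and a sentence explaining standardisation. No new data are needed. The team should confirm that the software named in the Analysis section can produce the standardised difference with clustered standard errors.

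### Sessions are randomised within hospitals, but no stated analysis uses session or hospital; the effect on the error rate is small at the plan's own ICC, and uncontrolled if the true ICC is larger

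*Protocol article*

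**What the plan says.** The Randomisation section sets the unit: "Randomization will be done with each session in an out-patient clinic as a cluster unit". It adds that "Currently there are 10 sessions per week per study site", that "5 sessions will be treated as intervention group and another 5 sessions will be treated as control group per week", and that the draw is "block randomization with each hospital as a block unit". With five hospitals this makes 10 x 5 = 50 weekly session slots.

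The Power calculation section recognises the clustering: "Accounting for the clustered randomized sampling design with 20 clusters (sessions) and an intra-class correlation of 0.002, 280 patients will be required per group". It gives no source for 0.002 and does not say whether 20 is the total or the number per arm.

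The Analysis section then fixes an unadjusted intention-to-treat comparison as primary: "The analysis will be performed using Pearson’s chi-square test or with the use of Fisher’s exact test", the latter when cells are small. Secondary outcomes are to be handled in a similar way. Crude odds ratios come from logistic regression and are set beside odds ratios adjusted for baseline variables such as sex, age, education and stage of readiness. Session and hospital are not mentioned. The promise in the Randomisation section to adjust for differences between groups concerns baseline imbalance, not clustering.

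**The concern.** Pearson's chi-square, Fisher's exact test and ordinary logistic regression all take patients as independent. Here patients are allocated in groups and the intervention is partly delivered in groups: the leaflet and warning are given in the consultation, and the Training and quality assurance section organises delivery by clinic session. If outcomes within a session are positively correlated, the patient-level standard error leaves out the between-session part of the variance. The p-value then does not carry its nominal 5 %, and any interval placed around the odds ratios shares the fault.

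This is not a detail left to an unseen analysis plan. The article names the primary test, and that test does not match the design or the sample-size reasoning in the preceding section. The analysis as stated would neither estimate the ICC nor allow for it, so the validity of the result depends on an unsourced value being right.

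**Working it through.** **Inputs.** Quit rates "29 % for the intervention group and 18 % for the control group", 5 % significance (taken as two-sided), power 0.80, 15 % attrition, ICC 0.002 and 20 clusters, all from the Power calculation section; 10 sessions at each of five hospitals, from the Randomisation section; 560 patients in total.

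**Step 1: reproduce the plan's sample size.** The pooled two-proportion formula without continuity correction gives 233 per group, as stated. For attrition, 233 / 0.85 = 274.1; the plan states 274. The cluster inflation is DE = 1 + (m - 1) x ICC, with m the patients per cluster:

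- 20 clusters per arm: m = 233 / 20 = 11.65, DE = 1.0213, and 233 x 1.0213 / 0.85 = 279.96. Inflating 274 instead gives 280.96.
- 50 sessions in total (25 per arm): m = 274 / 25 = 10.96, DE = 1.0199, and 274 x 1.0199 = 279.5.
- 20 clusters in total (10 per arm): m = 23.3, DE = 1.0446, giving 286.3; inflating 274 gives 288.5.

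So 280 fits 40 to 50 clusters in total. It does not fit 20 in total.

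**Step 2: true type I error of the stated test.** With N = 560 and equal clusters, m = 560 / K and alpha = 2 x (1 - Phi(1.96 / sqrt(DE))). For K = 50 at ICC 0.002: m = 11.2, DE = 1 + 10.2 x 0.002 = 1.020, sqrt(DE) = 1.010, alpha = 5.2 %.

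| Session ICC | 50 clusters (m = 11.2) | 40 clusters (m = 14) | 20 clusters (m = 28) |
|---|---|---|---|
| 0.002 (plan) | 5.2 % | 5.3 % | 5.6 % |
| 0.01 (assumed) | 6.2 % | 6.5 % | 8.2 % |
| 0.02 (assumed) | 7.4 % | 8.1 % | 11.4 % |
| 0.05 (assumed) | 11.1 % | 12.7 % | 20.1 % |

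At ICC 0.002, sqrt(DE) runs from 1.010 to 1.027, so intervals would be 1 to 3 % too narrow. A beta-binomial simulation (40,000 runs, 18 % quitting in both arms, 20 and 50 clusters) agrees to within about 0.3 percentage points.

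**Step 3: hospital blocking.** Step 2 ignores it. Sessions are balanced 5 to 5 within each hospital, so between-hospital variance largely cancels from the treatment contrast, while an unstratified test keeps it in the standard error. Simulating 5 hospitals x 10 sessions x 11 patients, 18 % quitting:

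- Session ICC 0.002: 5.4 % with no hospital variance, 4.7 % with an assumed hospital ICC of 0.05.
- Session ICC 0.01: about 6.1 to 6.2 % and 5.6 % respectively.
- Session ICC 0.05: still 10 to 11 %.

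**Step 4: does a valid test fit the planned sample?** In the step 2 simulations, a t-test on session-level proportions held 4.8 to 5.2 % throughout. With all 560 analysed and the plan's quit rates, its power at ICC 0.002 was 0.81 with 20 clusters and 0.85 with 50.

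**The case against.** The strongest reply concerns size. The only ICC in the document is 0.002, and with the cluster counts that reproduce 280 the error rate moves by 0.2 to 0.3 percentage points. Everything above 5.6 % rests on ICCs 5 to 25 times as large, which the document does not support. It also says that the same oncologists and nurses see both groups, which limits staff differences between sessions. Hospital blocking works in the conservative direction and can take the error below 5 % at the plan's ICC. All of this stands. The blocking argument does not remove the inflation at session ICCs of 0.01 and above.

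A second reply is that clusters may be tiny. If allocation were redrawn each week over the 78-week recruitment, there would be 50 x 78 = 3,900 session-weeks for 560 patients, about 0.14 each, and the inflation would be near nil. The per-week wording leaves this open. A single draw before the study and a count of 20 clusters point to fixed slots, but the article does not settle it.

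A reader might infer that the type I error certainly exceeds 5 %, or that it reaches 20 %. The first is not certain at the plan's own ICC, because of the blocking. The second needs an assumed ICC of 0.05 together with 20 clusters in total, the count that contradicts the plan's 280. A reader might also say that every confidence interval in the plan is wrong; the Analysis section mentions none, so only intervals computed later from the same models would be affected.

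**Conclusion.** The mismatch is real: the design and the sample size recognise clustering by session, the randomisation is blocked by hospital, and the stated analysis uses neither. At the plan's own inputs the consequence is small, with a type I error of about 5.2 to 5.3 %, or 5.6 % with only 20 clusters in total, and possibly no excess once the blocking is considered. The case for change is that the stated test gives no protection if 0.002 is too low: with 50 sessions the error is about 6 %, 7 % and 11 % at ICCs of 0.01, 0.02 and 0.05, and higher with fewer clusters. Those ICCs are assumptions. The figures also rest on fixed weekly session slots and equal cluster sizes; uneven recruitment across sessions would raise the design effect.

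**What to change.** Replace the primary test with one that respects the randomisation. Either of these would do:

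- a logistic GEE or mixed model with session as the cluster, hospital as a fixed effect and a small-sample correction; or
- a hospital-stratified analysis of session-level quit proportions.

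Use the same approach for the secondary outcomes and for the crude and adjusted odds ratios, and report the observed ICC. State whether the session allocation is fixed for the whole of recruitment or redrawn weekly, and reconcile the 20 clusters in the Power calculation section with the 10 sessions at five hospitals in the Randomisation section.

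The cost is a change of wording in the Analysis section, a session identifier kept in the dataset, and possibly slightly wider intervals. At the plan's own ICC no extra patients are needed. If the true ICC is larger, a valid test will have less power (with 50 sessions and 560 analysed, about 0.82 at 0.01 and 0.69 at 0.05), which reflects information that the patient-level test would wrongly claim to have.

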### Current study

The present study aims to test the effectiveness of a specially designed smoking cessation intervention using a risk communication approach for cancer patients who are smokers, to (i) achieve a higher quit rate, (ii) improve their smoking behaviour, (iii) motivate their intention to quit smoking, (iv) improve their risk perceptions of continued smoking, and (v) improve the quality of life.

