### Primary and secondary outcomes

The primary outcome is the self-reported 7-day point prevalence (PP) quit rate of the smoking cancer patients during 6-month follow up. The secondary outcomes include (a) self-reported 7-day PP quit rate at 12-month follow-up and the biochemically validated quit rate at 6-month follow-up (non-smoking status is confirmed by a carbon monoxide level in expired air < 9 ppm and saliva cotinine level < 115 ng/mL in parallel test), (b) percentage of patients reduced smoking by at least 50 % at 6- and 12-month follow-up compared to baseline, (c) percentage of patients with quit attempt(s) at 6- and 12-month follow-up, (d) change in the intention to quit smoking (stage of readiness to quit) at 6- and 12-month follow-up compared to baseline, (e) change in risk perceptions of continued smoking at 6- and 12-month follow-up compared to baseline, and (f) change in health-related quality of life at 6- and 12-month compared to baseline.

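### SF-12 quality of life is placed under an unadjusted approach whose only named outcome test is chi-square/Fisher, its definition differs between sections, and its baseline score is never a covariate

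*Protocol article*

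**What the plan says.** Improving quality of life is one of the five aims under Current study ("v) improve the quality of life"). Under Structured questionnaire the instrument is "quality of life (SF-12 v2"). Under Primary and secondary outcomes, item (f) is "change in health-related quality of life at 6- and 12-month compared to baseline".

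The Analysis section sets out the comparison in three steps:

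- It gives the type of analysis for the quit rate: "The primary analysis will be an unadjusted intention-to-treat analysis".
- It gives the test: "The analysis will be performed using Pearson’s chi-square test or with the use of Fisher’s exact test", with Fisher's test reserved for small cells.
- It extends this to the other endpoints: "Similar approach will be used to estimate the differences in secondary outcomes". The examples in brackets end with "and quality of life at 6 and 12 months) between groups".

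The t-test and the Wilcoxon test appear in the same paragraph, but only for comparing baseline characteristics. The only adjusted model is the logistic regression for quitting. The article gives no cut-off that would turn the SF-12 into categories.

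**The concern.** There are three linked problems.

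1. **Test and data type.** Chi-square and Fisher's exact test compare category counts. Applied to a score, they need categories that the article does not define. They ignore the ordering and give no mean difference. The article separates continuous from categorical methods at baseline, but then lists quality of life with binary endpoints under a sentence that follows chi-square/Fisher.
2. **Definition.** The outcomes section speaks of change from baseline, and the Analysis section speaks of the value at 6 and 12 months. In the same bracketed list, smoking reduction keeps its reference to baseline and quality of life does not.
3. **Baseline score.** The SF-12 is in the questionnaire and the outcome definition needs its baseline value, yet no stated analysis adjusts for it.

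At stake is the precision of the result on a stated aim. There is also room to choose after the fact between a follow-up comparison and a change comparison, which can differ when the arms differ by chance at baseline.

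**Working it through.** **The plan's own figure.** The article gives a sample size only for the quit rate: 29 % against 18 %, 5 % level, power 0.8, 233 per group. The two-sided pooled formula without continuity correction is

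n = [1.960·√(2·0.235·0.765) + 0.842·√(0.29·0.71 + 0.18·0.82)]² / 0.11² = (1.175 + 0.500)² / 0.0121 ≈ 232.1, rounded up to 233.

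This reproduces the stated figure, but it concerns the binary primary outcome. The article gives no effect size, SD, correlation or power for quality of life. The inputs below are therefore assumptions, shown over a range.

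**How the candidate analyses relate.** Let D0 and D1 be the between-arm differences in mean SF-12 at baseline and at follow-up.

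- Follow-up only: D1
- Raw change: D1 − D0
- Baseline-adjusted (ANCOVA): D1 − b·D0, where b is the within-arm slope of follow-up on baseline

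Under randomisation D0 is zero on average, so all three estimate the same effect. In any one trial they differ by multiples of D0.

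**Variance.** With equal SDs σ at both times and correlation ρ, the variances per patient are:

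- follow-up only: σ²
- raw change: 2σ²(1 − ρ)
- baseline-adjusted: σ²(1 − ρ²)

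The ratio of adjusted to follow-up only is 1 − ρ². The ratio of adjusted to change is (1 − ρ²)/[2(1 − ρ)] = (1 + ρ)/2.

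| ρ (assumed) | Adjusted / follow-up only | Reduction | Adjusted / raw change | Reduction |
|---|---|---|---|---|
| 0.3 | 0.91 | 9 % | 0.65 | 35 % |
| 0.5 | 0.75 | 25 % | 0.75 | 25 % |
| 0.7 | 0.51 | 49 % | 0.85 | 15 % |
| 0.8 | 0.36 | 64 % | 0.90 | 10 % |

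**What this means for power.** Assume a true difference of 0.25 SD, two-sided 5 %, 280 × 0.85 = 238 analysable patients per group, and no clustering. Power = Φ(0.25/√(2v/238) − 1.960), where v is the variance in units of σ².

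| ρ | Follow-up only | Raw change | Baseline-adjusted |
|---|---|---|---|
| 0.3 | 0.779 | 0.635 | 0.816 |
| 0.5 | 0.779 | 0.779 | 0.883 |
| 0.7 | 0.779 | 0.941 | 0.968 |
| 0.8 | 0.779 | 0.991 | 0.995 |

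Raw change has lower power than follow-up only when ρ is below 0.5 and higher power above it. The adjusted analysis has the highest power in every row.

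**The case against.** The strongest reply is that this is a condensed article and that a similar approach need not mean the same test. It can mean an unadjusted intention-to-treat comparison, with the test chosen by variable type. The authors plainly know that distinction, because they apply it at baseline. That is a fair reading, and on it the test for a score is merely unnamed, which an article may leave to the full protocol. The chi-square point then softens. The difference in wording between the two sections remains, and so does the unadjusted analysis.

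The wording in the Analysis section may also be shorthand for the change outcome. If so, the baseline score is used in forming the change, and it would be wrong to call it unused. It is still not a covariate, and raw change remains less precise than the adjusted analysis at every correlation examined.

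The Randomisation section promises to check the groups for differences and adjust for any that are found. It refers to socio-demographic profile, smoking history and clinical history, not the SF-12, and it depends on an imbalance being seen. It does not make baseline SF-12 a planned covariate.

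A reader might infer two stronger things:

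- **That the SF-12 will be dichotomised, for example at the median, with a large loss of information.** The article proposes no cut-off, so a loss worked out for such a split would size an analysis that nobody has stated.
- **That risk perceptions and stage of readiness are also assigned chi-square/Fisher.** They are defined as changes from baseline, but the examples in the Analysis section do not name them, so nothing is stated wrongly about their tests.

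**Conclusion.** The point holds as a moderate one about a secondary outcome. Read literally, the article puts a score under a test meant for categories. Read generously, it leaves the test open. On either reading the stated analysis is unadjusted, and the Analysis and outcomes sections describe the quality-of-life endpoint differently.

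The gain from adjustment is a variance reduction of 25 to 49 % against follow-up only and of 25 to 15 % against raw change, for ρ from 0.5 to 0.7. These figures rest on an assumed correlation, equal SDs, a linear relation and no allowance for clustering. The direction does not depend on the exact ρ within 0.3 to 0.8; the size does. Follow-up-only and raw-change comparisons are both unbiased under randomisation, so the case for adjustment is one of precision and clear prespecification, not of bias. The primary quit-rate analysis and the sample size are unaffected.

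**What to change.** Make three changes to the text:

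1. Align Primary and secondary outcomes with Analysis so that both describe the same quality-of-life endpoint. With baseline as a covariate, modelling change or the follow-up score gives the same adjusted arm difference, so one sentence can settle this.
2. State that SF-12 scores at 6 and 12 months are compared as continuous outcomes by ANCOVA or a linear mixed model, with the baseline score as covariate and allowance for the randomised session. Report the adjusted mean difference with its 95 % confidence interval.
3. Restrict chi-square/Fisher to the binary outcomes.

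Extending the baseline-adjusted approach to risk perceptions and stage of readiness (with a model suited to ordered stages) is optional.

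The cost is analysis wording. No new data, visits or patients are needed, because the change-from-baseline outcome already requires the baseline score.
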